**Fig. 2 Fig2:**
[figure not shown]
Participant timeline

#### Baseline (T0)

A message will be sent to the e-mail addresses participants provided through the website. This e-mail contains information about every part of the study, participation and privacy regulations. Every participant will get a personalized link to the baseline questionnaire (T0), where participants give their informed consent. At the end of this survey, participants will be asked to fill in their home address and phone number. These data will be added to the encrypted file with participant information. Then, a package will be sent to the given address, containing an information letter, an instruction manual with frequently asked questions (FAQs) about the diary period, and a closed colored envelope. This envelope contains either a blank individual or a dyadic planning sheet.

#### Intervention and diary period (T1)

A few days after sending this package, the intervention is offered by phone (more information below). After the intervention, participants are guided by the researcher to register their phone numbers on the website of the text message service (www.surveysignal.com). Participants get a few example questions, to practice filling in the diary, followed by instructions about the diary questionnaires. The day after filling in the planning sheet, the first text message will be sent by Survey signal. Every evening, for the following 21 days both partners get a text message with a link to the diary questionnaire. After 11 days, participants receive a motivating email, which states that they filled in half or more than half of the questionnaires and that we value their participation. When several diaries are missed, an email is send to ask if there are problems or if we can do anything to make their participation easier (e.g., changing the time of the text message). After completing the diary, participants receive a voucher of 20 euros as a compensation for their time.

#### Follow-up (T2)

Three months after the diary has ended, couples receive an email with a follow-up questionnaire (T2). Reminders will be send to increase the response rate. When both partner fill in this questionnaire, they will receive a second compensation, again a voucher of 20 euros. At the end of the questionnaire, participants will be debriefed and given information on how to receive the study results.

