## Methods

### Participants

Participating couples must consist of one smoker (smoking cigarettes every day or multiple days per week) and one non-smoker, who are in a relationship for at least one year and living together. Both partners should have their own mobile phone, for receiving the daily questionnaire. Exclusion criteria are pregnancy and aged younger than 18. Participants from the Netherlands can enroll from April 2017 to July 2018.

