### Randomization

Couples are randomized by the researchers by means of flipping a coin. Conditions are predetermined (before registration of the couple) by this method for every block of ten couples, to exclude any kind of influence the researchers might have. The randomization is single-blind; couples do not know that there are two different conditions until the debriefing that is given after the follow-up questionnaire. When participants do not fill in the follow-up questionnaire, the debriefing is sent to them by e-mail.

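### Debriefing at the end of the T2 questionnaire is not held until both partners have answered, so the second respondent may lose the single blind at 3 months

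*Protocol article*

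**What the plan says.** The Randomization section defines the blind: "couples do not know that there are two different conditions until the debriefing that is given after the follow-up questionnaire". The Follow-up (T2) section places that debriefing inside the T2 step: "At the end of the questionnaire, participants will be debriefed and given information on how to receive the study results". People who never complete T2 are handled separately: "When participants do not fill in the follow-up questionnaire, the debriefing is sent to them by e-mail".

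Both members of the couple answer T2. Table 1 has separate follow-up columns for smoker and partner, and the items differ in part (smoking dependence, for example, is asked of the smoker only). Number of cigarettes, duration of abstinence and relationship satisfaction are asked of both. The second voucher depends on both replies: "When both partner fill in this questionnaire, they will receive a second compensation, again a voucher of 20 euros". Late replies are chased: "Reminders will be send to increase the response rate". Eligible couples are those "who are in a relationship for at least one year and living together".

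Under Statistical analyses, the primary outcome is the proportion abstinent at days 7, 14 and 21 and after 3 months. Strengths and limitations acknowledges that outcomes rest on self-report alone.

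**The concern.** The blind consists of couples not knowing that a second condition exists, and the debriefing is what ends it. If the debriefing appears when one respondent reaches the end of the survey, it can reach one half of a couple while the other half still has to answer. The two live together, and the voucher rule gives the first finisher a reason to bring up the questionnaire.

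At stake is the T2 data of the second respondent. Three-month abstinence, its duration and relationship satisfaction are all self-reported, with no objective check on smoking. Someone who has just learned that the trial compares planning together with planning alone, and which of these the couple received, could answer differently by arm. Concealing the existence of two conditions is the only participant blinding the article describes, so it is worth keeping intact until the last T2 answer is in.

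**Working it through.** **Step 1. Does the text hold the debriefing back?** Set side by side, Randomization ends the blind at the debriefing, and Follow-up (T2) gives the debriefing when the questionnaire ends. Table 1 shows two respondents per couple. No sentence makes the debriefing wait for the second respondent or asks the two to answer at one sitting. The e-mail rule for non-completers is worded by participant, which fits release person by person. The surveys are online (Data management), and a closing page normally appears when that respondent finishes. Release per person is therefore the natural reading, but it is inferred. Individual links are stated only for baseline: "Every participant will get a personalized link to the baseline questionnaire (T0), where participants give their informed consent".

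**Step 2. Which data are exposed?**

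| Order of T2 completion | Disclosure before the second answer? | Exposed T2 data |
|---|---|---|
| Non-smoker first | Yes | Smoker's abstinence, cigarettes, duration of abstinence, relationship satisfaction |
| Smoker first | Yes | Partner's reports of cigarettes and duration of abstinence, partner's relationship satisfaction |
| Either order | No | None |
| Both together | Not applicable | None |

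The diary comparisons at days 7, 14 and 21 are complete about three months before T2 is sent, so debriefing cannot touch them. Nor can it change smoking that has already happened; only reporting at T2 is open to it.

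**Step 3. The plan's own figure.** The illustration below uses the planned 70 per group, so that is checked first. Inputs from Power analysis: 15% in the control group, an increase of 20% read as 15% to 35%, alpha 0.05 (taken as two-sided), power 0.80. With unpooled variance,

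n = (1.960 + 0.842)² × (0.15×0.85 + 0.35×0.65) / 0.20² = 69.66, rounded up to 70.

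The stated figure reproduces.

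**Step 4. Illustration of size; inputs assumed, not in the documents.** Let q be the share of smokers who answer T2 after hearing the debriefing content (taken as equal in both arms), and b the between-arm difference in reporting shift among them. The shift in the 3-month difference is q × b. The last column is the chance of a nominally significant result in the direction of the shift when there is no true effect: 70 per arm, 15% base rate, two-sided alpha 0.05, normal approximation. With no shift it is 2.5%.

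| q | b | q × b (points) | Chance |
|---|---|---|---|
| 0.10 | 0.05 | 0.5 | 3.0% |
| 0.25 | 0.05 | 1.25 | 3.9% |
| 0.25 | 0.10 | 2.5 | 5.9% |
| 0.50 | 0.05 | 2.5 | 5.9% |
| 0.25 | 0.20 | 5 | 11.8% |
| 0.50 | 0.10 | 5 | 11.8% |
| 0.50 | 0.20 | 10 | 31.4% |

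A 5-point shift in the whole arm needs b = 0.05/0.50 = 10 points to 0.05/0.25 = 20 points among exposed smokers. With b = 5 points and the same exposure, the shift is 1.25 to 2.5 points and the chance about 4% to 6%.

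**The case against.** The strongest reply is that the article does not say each person is debriefed on finishing. It describes the T2 invitation and the blind in terms of couples, and the release of a survey's end page is a detail that a condensed article may leave out. That stands as a limit on certainty: release per couple is not excluded. It does not remove the point, because the article does state when the debriefing is given, and as stated the timing does not secure the blind it claims.

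A reader might infer that the blind is broken at the primary endpoint. The documents do not support that. For the smoker's report to be affected, the partner must finish first, the two must answer at different times, and the partner must pass on the content before the smoker answers. The voucher gives a reason to prompt a reply, not to explain the design. The weekly abstinence comparisons are untouched in any case.

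A reader might also infer a false-positive rate near 12%. The arithmetic is right, but it requires a net 10 to 20-point reporting shift among exposed smokers when 25% to 50% are exposed, and nothing in the documents supports that.

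It is also fair to say that participants already know what they did in the planning call, so debriefing adds only that another condition existed, and that people in both arms could learn this. The direction of any bias is therefore open. This limits the likely harm without excluding it, since the outcome is unverified self-report.

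**Conclusion.** The point holds as a gap in how the blind is protected at T2. As written, the second partner to respond can learn of the two conditions before answering, and the single blind may be lost for that person at 3 months. This rests on two things: the inferred but natural reading that the debriefing is shown to each respondent on finishing, and cohabiting partners sometimes answering at different times and talking in between.

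The smoker's 3-month abstinence report is exposed only when the non-smoker finishes first and discloses. When the smoker finishes first, the exposure is confined to the partner's T2 reports. The documents give neither the exposed share nor any reporting shift, so size and direction cannot be determined. The 0.5 to 10 point range follows only from the assumed inputs. The case for acting is that prevention costs almost nothing, not that a large bias has been shown.

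**What to change.** Remove the debriefing from the end of the T2 questionnaire. Send it by e-mail, the route already used for people who do not complete T2, to both partners together once both have answered or the T2 reminder period has closed. State this rule under Follow-up (T2) and Randomization. The cost is an edit to the survey's closing page, one e-mail per couple, and a short delay in debriefing for the first finisher. The sample size does not change.

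For couples already debriefed under the current rule, keep the intention-to-treat analysis as primary. If completion times were stored, report response order by arm descriptively, noting that order arises after randomization and does not show whether anything was disclosed. Do not rely on an analysis that drops smokers who answered second. Response order may be related to relapse or motivation and may differ by arm, so dropping them could introduce selection bias, and it would depart from the planned intention-to-treat approach.

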### Randomization

Couples are randomized by the researchers by means of flipping a coin. Conditions are predetermined (before registration of the couple) by this method for every block of ten couples, to exclude any kind of influence the researchers might have. The randomization is single-blind; couples do not know that there are two different conditions until the debriefing that is given after the follow-up questionnaire. When participants do not fill in the follow-up questionnaire, the debriefing is sent to them by e-mail.

### Detailed description of intervention and groups

The intervention is based on a planning sheet originally used to enhance pelvic floor exercise after prostatectomy among prostate cancer survivors [17]. Participants were asked when and where they were going to perform these exercises. Because quitting smoking is a different kind of behaviour, the sheet was adapted. Instead of focusing on starting with a health enhancing behaviour, it is focused on stopping an unhealthy behaviour. Text and examples were adapted to fit the situation of a smoker and we ask participants to sign the plan to make it more official. The main idea, of creating implementation intentions, remained the same.

### Condition 1: Dyadic planning intervention

The couple is asked to open the colored envelop and read the instructions out loud, so the researcher on the phone is also able to hear in which step the couple is. The first step is to write down moments that the smoker usually smokes. The partner is invited to help and also think of moments that might have been forgotten. If the partner does not involve him or herself in the task, the researcher will ask if he or she has any additions. The researcher makes sure that the list of moments is complete, for example by asking when the first and last cigarette on a day is smoked and whether there are any important moments that occur less frequently (e.g., birthdays, going out). The second step is writing down where these moments occur, and how to prevent smoking at these moments. Again, partners are asked to help the smoker. Plans have to be concrete actions; this is monitored by the researcher. For every moment a plan is made (e.g., going for a walk instead of smoking after lunch). Finally, the couple indicates how feasible each plan is on a scale from 1 to 5. On the last page of the planning sheets, the smoker writes down the quit date (the next day), and both partners put their signature to make it ‘official’. They are asked to take a picture of the plan and email it to us, when possible, during the phone call.

### Condition 2: Individual planning intervention

When the non-smoking partner is next to the smoker, the researcher asks him or her to leave the room and not be present while filling in the planning sheet. Then, the smoker is asked to open the colored envelope, and read the instructions out loud. The planning sheet and steps are similar to the dyadic planning condition, the only difference being the partners’ absence during the intervention. Therefore, only the smoker makes and signs the plan. When the smoker has sent the plan by email, the partner can reenter the room for the diary instructions.

### Measures

Table 1 shows all variables that are measured (including exploratory/potential covariates).

**Table 1 Tab1:** Content of the baseline, diary and follow-up questionnaire

Measures	Baseline		Diary		Follow-up	
	*Smoker*	*Partner*	*Smoker*	*Partner*	*Smoker*	*Partner*
Baseline information						
Socio-demographics	X	X				
Smoking details and history	X	X			X	
Quit attempt history	X					
Primary & Secondary outcomes						
Number of cigarettes smoked	X		X	X	X	X
Hiding of smoking	X				X	
Duration of abstinence					X	X
Perceived frequency of smoking-related conflicts (SRC)	X	X			X	X
Relationship satisfaction	X	X	X	X	X	X
Smoking dependence	X		X	X	X	
Smoking now compared to before quit attempt					X	X
Mediators						
Details of partner contact			X	X		
Partner responses			X	X		
Partner responses to difficult moment			X	X		
Exploratory outcomes and potential covariates						
Attitude towards smoking	X	X				
Affect (PANAS)	X	X	X	X		
Opinion partner about quitting/smoking behaviour	X	X				X
Influence of SRC	X					
Perceived susceptibility	X	X			X	X
Perceived relatedness	X	X			X	X
Self-compassion towards relapse			X	X	X	X
Intention to quit	X				X	
Taking steps to go smoking			X			
Use of smoking replacement			X	X	X	X
Difficulty quitting			X	X		
Adherence to planning			X	X	X	X
Helpfulness of planning			X	X	X	X
Conflicts not related to smoking			X	X		
Interference of quitting with relationship			X	X		
Details social contacts			X	X		
Interference of quitting with social contact			X			
Other health behaviours	X	X				
SRC initiator	X	X				
SRC recentness	X	X				
SRC pattern	X	X				
Partner interaction questionnaire	X	X				
Details most difficult moment			X	X		
Distraction from smoking			X	X		
Motivation to remain quit			X			
Evaluation of diary			X	X	X	X
Self-efficacy to quit	X		X	X		
Daily activities			X	X		
Role of smoking in break-up					X	X
Influence of plan on relationship					X	X
Missing smoking					X	

#### Primary outcomes

The primary outcome is self-reported smoking abstinence from tobacco smoking. Every day, participants are asked whether they smoked and if so, how many cigarettes (1, 2, 3, 4, 5, > 5). In the follow-up questionnaire, participants are asked about their smoking behaviour to assess effectiveness over time.

#### Secondary outcomes

In the baseline and follow-up questionnaire, participants fill in the Dutch version of the Maudsley Marital Questionnaire [26, 27]. The scale contains 15 questions that are answered on 9-point Likert scales (e.g., ‘How much are you committed to this marriage?). Daily relationship satisfaction is measured by asking participants how satisfied they are with their relationship at that moment. The scale ranges from 1 = ‘Unhappy’ to 10 = ‘Very happy’.

#### Mediators

Daily partner interactions (supportive behaviours and negative responses) will be examined as a possible mediator in the relationship between the intervention and the primary outcomes. First of all, participants are asked whether they had contact with their partner today (e.g., talking, texting). If they had contact, they are asked how satisfied they are about this (1 = ‘Not at all’ to 7 = ‘Very much’). Details are asked about the time spent with the partner (e.g., how much time, when during the day). Supportive behaviours and negative responses are measured by seven questions about interactions about smoking and the planning (e.g., today my partner motivated me to remain abstinent, today my partner did not show interest in my planning, today my partner and I had a fight about my planning). The answer scale ranges from 1 = ‘Not at all’ to 7 = ‘Very much’. Participants are asked whether they discussed the most difficult moment of that day with their partner, and if so how he/she responded. Partner responses (supportive and negative) to difficult moments are measured by four items (i.e., supportive, motivating, angry/irritated, blaming) and participants are asked to score these on a scale from 1 = ‘Not at all’ to 7 = ‘Very much’.

### Data management

Online data is collected on the secured and password protected server of Unipark [28] and regular (anonymous) back-ups are saved on the secured and password protected server of the University Medical Center Groningen, only assessable by the involved researchers. The surveys are online and programmed in such a way that no questions can be skipped or answered different than the scale, therefore, range checks are not necessary. Data will be monitored for missing days during the study period.

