### Power analysis

In literature, 15.48% of the participants successfully quit smoking after an intervention using implementation intentions, measured one month later [3]. Therefore, we expect an abstinence rate of 15% in the individual planning (control) group. With a power of 0.8 and an alpha of .05, we need 70 couples per group to detect a relevant increase in effectiveness of 20% (primary aim). Additionally, we consider a minimal decrease of 50% in number of cigarettes, between baseline and follow-up, relevant [30].

A minimum sample of 50 cases is advised in a multi-level design [31] and diary studies in this research area are usually between 60 and 100 participants. Considering a power of .80 and an alpha of .05, the power analysis showed that a net sample size of 82 couples is sufficient to find an effect size of at least .3 (a medium effect) in the diary between smoking-related interactions and smoking behaviour (secondary aim). Therefore, with the sample of 140 couples we have sufficient power to detect a relevant difference in effectiveness of the intervention as well as the research questions related to the diary data. To take into account drop-out, we aim to include 15% extra couples.

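### As described, self-reported 3-month abstinence comes only through a 19-measure, forced-answer e-mailed questionnaire, with no short contact for smokers who do not complete it

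*Protocol article*

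**What the plan says.** The Primary outcomes section defines the endpoint: "The primary outcome is self-reported smoking abstinence from tobacco smoking". For the later time point it adds: "In the follow-up questionnaire, participants are asked about their smoking behaviour to assess effectiveness over time". The Statistical analyses section compares abstinence at days 7, 14 and 21 and at 3 months, and bases the primary analyses on baseline and follow-up data under intention to treat.

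The Follow-up (T2) section sends the questionnaire by e-mail three months after the diary. It names two retention measures: "Reminders will be send to increase the response rate", and a 20-euro voucher paid when both partners respond. The Randomization section adds that couples who do not fill in T2 are e-mailed the debriefing, which reveals that there were two conditions.

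The Data management section says that the surveys are "programmed in such a way that no questions can be skipped". In Table 1, 19 measures are marked for the smoker at follow-up. They include hiding of smoking, smoking-related conflicts, the role of smoking in a break-up, and relationship satisfaction, which at T2 is a 15-item scale. The partner is also marked at follow-up for number of cigarettes and duration of abstinence.

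Other channels exist. Phone numbers are collected at baseline, the intervention is given by phone, and in the diary period "for the following 21 days both partners get a text message with a link". On losses, the Power analysis section says: "To take into account drop-out, we aim to include 15% extra couples".

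**The concern.** The primary analysis needs one answer at 3 months: is the smoker abstinent? As described, the smoker can give it only by going through a long form with mandatory answers, several of them on sensitive subjects. Someone who has relapsed, or whose relationship is strained, has reasons to leave the form unopened or to stop part-way. A strained couple may also miss the voucher, because it depends on both partners.

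Non-response related to relapse is plausible, though the article gives no data on it. If it occurs, it biases the estimated abstinence rates. Because the intervention changes how far the partner is involved, non-response could also differ by arm. Recruiting extra couples restores numbers but does not remove that bias.

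Timing matters too. Once the debriefing has gone out, the smoker knows there were two conditions, so an abstinence answer obtained later is no longer blinded. A fallback has to be planned before that step.

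**Working it through.** **1. The plan's own sample size.** Inputs from the Power analysis section: 15% abstinence in the control arm, an increase of 20% read as 20 percentage points (15% vs 35%), power 0.80 and alpha 0.05 (two-sided assumed).

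n per arm = (1.960 + 0.842)² × (0.15×0.85 + 0.35×0.65) / 0.20² = 69.66, so 70. This matches the stated 70 per group, 140 in total.

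**2. The loss that the plan absorbs.** 140 × 1.15 = 161 couples. (161 − 140)/161 = 21/161 = 13.0%. This is the allowance, not a forecast of T2 non-response; the article gives none.

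**3. What a missing T2 could do to the estimate.** Assume the same fraction m missing in each arm, and 15% and 35% abstinent among responders, so the complete-case difference is 20 points.

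- If every non-responder smokes, the true rates at m = 0.13 are 0.87 × 15 = 13.05% and 0.87 × 35 = 30.45%. The true difference is 17.4 points and the complete-case bias is 20 − 17.4 = 2.6 points.
- The lower extreme has all missing dyadic smokers smoking and all missing individual smokers abstinent: 17.4 − 13 = 4.4 points.
- The upper extreme is the reverse: 17.4 + 13 = 30.4 points.

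In general the bias in the all-smoking case is 20m points, and the bounds are 20(1 − m) ± 100m points:

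| Missing per arm (assumed) | Bias if all non-responders smoke | Extreme bounds on the difference |
|---|---|---|
| 5% | 1.0 | 14.0 to 24.0 |
| 6.5% | 1.3 | 12.2 to 25.2 |
| 13% | 2.6 | 4.4 to 30.4 |
| 20% | 4.0 | −4.0 to 36.0 |
| 30% | 6.0 | −16.0 to 44.0 |

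The 6.5% row is the 13% row with half of the missing answers recovered, which is also an assumption.

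**4. Power with 161 couples** (same formula, 15% vs 35%). As complete cases: 0.802 at 13% missing, 0.793 at 15%, 0.712 at 30%. With missing counted as smoking: 0.800 at 10%, 0.769 at 15%, 0.662 at 30%. If half of the missing outcomes were recovered, complete-case power would rise from 0.793 to 0.826 at 15% missing, and from 0.712 to 0.793 at 30%.

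**5. Single-item refusal.** No figure can be put on this. It costs the outcome only if the smoking item follows the refused one or unfinished forms are dropped. Table 1 is grouped by topic and is not a questionnaire order.

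**The case against.** The strongest reply is that much of the mechanism lies outside the article. Item order, saving of partial answers, a possible no-answer option and the tracing of non-responders are operational details that a condensed article may leave out. The channel and content of the reminders are not given either. This stands in part. A reader might infer that refusing any one item forfeits the primary outcome; the article does not support that, and it can be said only conditionally.

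A reader might also infer that smoking status cannot be learned in any other way. That goes too far, because the partner separately reports cigarettes and abstinence at T2. However, the endpoint is defined as self-report, no substitution rule is stated, and the partner's form comes by e-mail with forced answers too. The trial also measures hiding of smoking, so the partner may not know. The comparisons at days 7, 14 and 21 do not depend on T2, but the primary analyses are stated to use baseline and follow-up data.

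The reminders, voucher and drop-out allowance are real safeguards and should be credited. Forced response is also a deliberate choice that buys complete forms.

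On size, it is tempting to say that the result could move by 13 points. That needs every non-responder in one arm to be abstinent and every one in the other to be smoking. Under the more natural worry, equal loss made up of relapsed smokers, the bias is 2.6 points.

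What survives is not mere silence. The article fixes an e-mailed form with mandatory answers, and it does say what happens to non-responders: they are debriefed.

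**Conclusion.** The point holds in a limited form. A smoker who does not complete T2 has no self-reported 3-month outcome under the procedures described. One who refuses a single item can lose it, depending on item order and handling of partial forms, which are not stated.

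With 13% missing per arm, the likely distortion is modest (about 2.6 points if all non-responders smoke). The range that the data could not rule out is wide: about 4 to 30 points around a difference the trial is sized to detect at 20. Both figures rest on assumed, equal missingness and on 15% vs 35% among responders. If the analysis counts missing as smoking, the 2.6-point bias disappears in that scenario, but the bounds stay as wide. The plan contains no arithmetic error on this point. It is a worthwhile, inexpensive improvement in how the primary outcome is collected.

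**What to change.** 1. Ask smoking status at the start of T2, store it when that page is submitted, and allow a no-answer option on the non-primary items.
2. After the last reminder and before the debriefing, send each non-responding smoker one text through the existing diary service. It should ask only the primary abstinence question, worded as in T2. Count the answer as the primary outcome and record the mode of collection.
3. State whether the partner's T2 report is ever used when the smoker's answer is missing.

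The cost is a change to the survey set-up and, at the assumed 13% loss, about 20 messages (21 of 161 couples), with no extra staff. The downside is a few blank secondary items and a few primary answers collected by a different mode, which the recorded mode lets the analysis examine.
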